## Abstract

**Objectives:**

Over 9000 patients are diagnosed with oesophageal cancer annually in the United Kingdom (UK). Decision-making about treatment options is influenced by radiological staging, which may include computed tomography (CT), positron emission tomography (PET), and endoscopic ultrasound (EUS). The use of EUS varies considerably around the UK and, since the introduction of PET-CT, the added value of EUS has been questioned. The VALUE study aims to understand this variation and determine how often and why EUS changes treatment decisions. VALUE will also evaluate patient and clinician experiences and opinions of EUS.

**Methods:**

This is a prospective, observational study investigating EUS in oesophageal cancer staging. Patients will be recruited at up to eleven sites in the UK, where they will be consented (if eligible) and registered onto iMedidata RAVE. Clinical and demographic data, TNM staging, pre and post EUS treatment decisions, and complications will be collected. We will attempt to sample patients from ethnic minority backgrounds in the study population, as they are underrepresented in research. Up to 30 patients and 30 clinicians will be interviewed to evaluate the use of EUS and experiences of both patient and clinician. The primary endpoint is the proportion of cases that EUS changes treatment decisions. Secondary endpoints include identification of factors that clinicians’ and patients consider when deciding if EUS should be used, the time from diagnosis to treatment decision before and after EUS, and the reasons why EUS changed management. The study has been registered on Clinicaltrials.gov: NCT06440174. The trial is open to recruitment.

**Results:**

In total, 180 patients with potentially curable oesophageal cancer who are suitable for EUS will participate. Recruitment is currently planned until September 2025 and study results will be reported after June 2026.

**Conclusion:**

The VALUE study will enable a better understanding of how and why EUS is used in oesophageal cancer. This research will identify important factors that clinicians and patients consider when deciding EUS use and determine the frequency that EUS changes treatment decisions in the modern staging pathway.

**Advances in knowledge:**

The VALUE study is a prospective, multi-centre observational study investigating the use of EUS in the modern era of oesophageal cancer staging. The study aims to determine how often and why EUS changes treatment decisions. A qualitative component will explore both clinician and patient attitudes towards EUS.

## Introduction

Over 9000 patients are diagnosed with oesophageal cancer in the United Kingdom (UK) annually. The prognosis of these patients is poor, with an overall 5-year survival rate of 15%.^1^ Most patients (60%) present with advanced disease and palliation is the only treatment option. Accordingly, oesophageal cancer has considerable unmet research need.^2^

Shared decision-making about treatment options in oesophageal cancer is largely influenced by radiological staging, which inform clinicians of the likely disease extent,^3^ in combination with histopathology, and patient factors. Radiological staging may include computed tomography (CT), positron emission tomography (PET), and endoscopic ultrasound (EUS) which provide complementary information, yet each are affected by technical limitations. These tests help determine whether radical treatment is attempted, using either curative surgery or definitive chemoradiotherapy, or if palliation is most appropriate.

CT is a standard staging investigation for all patients with oesophageal cancer, and PET-CT is recommended in patients with potentially curable disease,^4^ except in suspected T1 tumours.^5^ In contrast, national guidance for EUS staging is less clear, and as a result, there is considerable variation in EUS utilisation. A survey of oesophageal cancer multi-disciplinary team (MDT) leaders across the UK,^6^ including 35 responses representing 97 UK NHS trusts, found that 29% recommended EUS for all potentially curable patients, whereas 46% requested EUS after PET-CT on a case-by-case basis. 20% reported both a lack of utility and concerns about treatment delay. 63% and 43% routinely use EUS for radiotherapy and surgical planning, respectively. Data from the National Oesophago-Gastric Cancer Audit (NOGCA) demonstrate a decline in EUS use from 62% of all patients in 2013, to 39% in 2019, and 18.6% to 2021,^7^ although there may have been an impact of the COVID-19 pandemic on the 2021 data. In 2020/21, EUS was used in 23.6% of patients who had a curative treatment plan.

Whilst the use of EUS is declining, the use of PET-CT for oesophageal cancer staging is increasing.^7^ However, evidence for this change in practice is limited. It is unclear whether reduced EUS utilisation is due to capacity constraints, and is therefore being used pragmatically, rather than in all patients who may benefit.^8^

National variation in staging pathways is undesirable. Patients should not undergo tests from which they do not benefit nor have treatment unnecessarily delayed. Equally, inconsistent radiological staging could cause variable patient selection for radical treatment, or variable delivery of treatment. There are also cost implications for healthcare services which should make responsible use of its resources. Therefore, the issue of unequal access to diagnostic tests must be addressed.

VALUE is a prospective observational study investigating EUS in the modern era of oesophageal cancer staging. A quantitative study component will examine how often and why EUS changes treatment decisions after initial staging with CT and PET-CT. A qualitative study component will explore both clinician and patient attitudes and opinions towards the utility of EUS in the staging pathway.

## Methods

### Study design

Co-ordinated by the Cancer Research UK Southampton Clinical Trials Unit, this is a prospective, multi-centre, observational cohort study using a mixed-methods design (Figure 1). Both quantitative and qualitive components are planned within VALUE (REC: 24/WS/0021). In total, 180 patients with biopsy-confirmed oesophageal or junctional cancer who are deemed to have potentially curable disease, and who are intended to receive EUS as part of their standard of care staging pathway, will be recruited from clinical centres in the UK. Up to 30 clinicians who regularly care for oesophageal cancer patients in a multi-disciplinary setting and up to 30 patients will be interviewed to gather their opinions and experiences of EUS. In the context of PET-CT, EUS is considered stage 2b following the model suggested by the IDEAL framework.^9^ The study is being sponsored by University Hospital Southampton and ethically approved, by the West of Scotland Research Ethics Committee. The NIHR has funded the study (NIHR reference number: 204931).

**Figure 1. tzaf012-F1:**
[figure not shown]
Trial schema.

### Participant screening

Patients will be recruited through MDTs at participating secondary care centres in the UK. Those deemed suitable for the study will be approached by their direct care team to participate. Eligibility criteria are listed in Table 1. Patients will be screened for eligibility, consented, and registered on the trial specific electronic Case Report Form (eCRF), where EUS is recommended. All patients will have the following data collected at screening to confirm eligibility; informed consent (can be received remotely), eligibility evaluation, medical history, Eastern Cooperative Oncology Group (ECOG) performance status 0-2, and clinical staging of disease by CT scan (if applicable). Patients may undergo PET-CT before EUS referral or before consent. Patients who have definite M1 disease on PET-CT, or a total length of disease deemed unsuitable for planned radical treatment by the MDT, are not eligible. The patient will be asked for consent to take part in the research before the EUS procedure (supplementary material). We ask that patients have at least 24 h to read the patient information sheet before giving consent, but can give consent on the day of the EUS, provided they have read the patient information sheet at least 24 h prior. To take part in the qualitative interviews, patients will sign an optional part of the consent form which will give the qualitative researcher permission to invite them to interview.

**Table 1. tzaf012-T1:** Eligibility criteria.

Inclusion criteria	Exclusion criteria
Patients aged 16 or above with first diagnosis of biopsy-confirmed oesophageal cancer Referred for EUS examination as part of standard of care investigations Tumour location in the oesophagus, or gastro-oesophageal junction (Siewert types I-III) MDT decision that patient is potentially curable with radical treatment (e.g., endoscopic treatment, surgery +/− neoadjuvant therapy, or definitive chemoradiotherapy) Eastern Cooperative Oncology Group (ECOG) performance status 0-2 Either: Clinical staging of T1 disease (CT and PET-CT are not required) Or: Clinical staging of T2-T4, N0-N3, M0 disease confirmed by CT scan. Adenocarcinoma or squamous cell carcinoma (SCC) histopathological cell type	Recurrent or residual disease Known distant metastatic disease Previous oesophagectomy or oesophageal radiotherapy Unable to undergo EUS examination Other histopathological cell type

### Quantitative study

#### Primary objective

To determine the proportion of cases in which EUS changes disease management.

#### Secondary objectives

To determine how and why EUS changed the management.To determine time from diagnosis to treatment decision before and after EUS.

#### Data collection

The following information will be entered onto the eCRF following the EUS procedure:

EUS report (details of what is recorded in the report should be recorded in Rave)Post EUS Treatment Plan agreed with patient.EUS complications (bleeding, infection, damage to teeth, aspiration, adverse reaction to sedation, perforation). Any complications occurring within the first 2 weeks following EUS will be recorded.If the treatment plan changed, details of reason(s) why EUS +/− FNA changed the treatment plan should be recorded.

Details of the treatment the patient receives will be recorded, and could include surgery, chemoradiotherapy (CRT) or chemotherapy. Data will be added within 6 months of registration.

Participation data will be entered remotely at site and retained with current data protection regulations. The principal investigator (PI) at each site is responsible for ensuring the accuracy, completeness and timelines of the data entered. Each participant is assigned a participant identifier code which is used to identify the participant during trial between the SCTU and site.

#### Primary endpoint

Percentage of patients where treatment plan changes post-EUS.

#### Secondary endpoints

To identify factors that clinicians and patients consider when deciding whether EUS should be used.How and why EUS changed the management.Time from diagnosis to treatment decision before and after EUS.

### Statistical analysis

#### Primary endpoint

We will compare the proportion of cases where EUS changes MDT decision against a null hypothesis of 5% with a one-sided test. We will also present 90% confidence intervals around the estimated proportion using the Wilson method.

#### Secondary endpoint

Where management was changed, we will tabulate reasons for how and why using descriptive statistics. We will calculate the time from treatment decision prior to EUS to treatment decision post EUS to measure the delay generated by waiting for an EUS. We will investigate whether patient and/or centre factors are associated with longer delay using cox regression methods with centre as a shared frailty.

#### Sample size calculation

The sample size is based on estimating the proportion of cases that EUS (when recommended) changes MDT decisions regarding treatment. We will test the observed proportion against a null hypothesis of 5% (considered too small to be of clinical use) using an alternative hypothesis of 10% (considered to be the level at which EUS may be beneficial). With 180 participants, we have 85% power based on a one-sided test with 5% type I error rate (STATA SE 18).

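### The stated pair of 85% power and 5% one-sided type I error at n=180 is a large-sample approximation that no binomial cut-off delivers

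*Protocol article*

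**What the plan says.** The Sample size calculation section of the protocol article sets the null hypothesis: "We will test the observed proportion against a null hypothesis of 5% (considered too small to be of clinical use". The alternative is a true proportion of 10%, taken as the point from which the procedure could be worthwhile. The design properties follow: "With 180 participants, we have 85% power based on a one-sided test with 5% type I error rate (STATA SE 18".

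The Primary endpoint paragraph under Statistical analysis plans to compare the observed share of changed MDT decisions "against a null hypothesis of 5% with a one-sided test". On the interval, the same paragraph says: "We will also present 90% confidence intervals around the estimated proportion using the Wilson method".

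Neither section says whether the test is a score (normal-approximation) test or an exact binomial test, and neither gives the number of changed decisions at which the null would be rejected. The article says that a detailed statistical analysis plan will be written before database lock. That plan is not shown.

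**The concern.** With 180 patients and a null proportion of 5%, only 180 × 0.05 = 9 changed decisions are expected under the null. At that count the binomial distribution is skewed and moves in visible steps. Moving the cut-off by one patient shifts the type I error by about 3 percentage points and the power by about 6.5. A power figure from a continuous normal curve can then describe a test that does not exist at the stated error rate.

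What is at stake is a stated property of the study's only primary hypothesis test. The study will either reject a 5% truth more often than the stated 5%, or have less power than the stated 85%. The choice between the two rules decides the conclusion at exactly 14 changed decisions, so it should be fixed before the data are seen.

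**Working it through.** **Inputs** (protocol article, Sample size calculation): n = 180, p0 = 0.05, p1 = 0.10, one-sided α = 0.05, stated power 85%. The 90% Wilson interval comes from the Primary endpoint paragraph under Statistical analysis. All 180 patients are taken as evaluable.

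**1. Reproducing the stated figure.** One-sample score test, normal approximation:

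power = Φ{[(p1 − p0) − 1.645·√(p0(1 − p0)/n)] / √(p1(1 − p1)/n)}

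- √(0.05 × 0.95/180) = 0.01625, and 1.645 × 0.01625 = 0.02672
- √(0.10 × 0.90/180) = 0.02236
- (0.05 − 0.02672)/0.02236 = 1.041, and Φ(1.041) = 0.851

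Power is 85.1%. Solving the same formula for n at 85% power gives 179.2, rounded up to 180. Other formulas tried do not give 85%: continuity-corrected 82.0%, arcsine 82.6%, Wald 72.3%, two-sided score 79.2%. The score formula is the evident source.

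**2. What that test does with whole patients.** Its critical proportion is 0.05 + 0.02672 = 0.07672, and 180 × 0.07672 = 13.8, so it rejects at 14 or more. Exact binomial tail probabilities for X, the number of changed decisions:

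| Reject at | P(X ≥ cut-off), p = 5% (type I error) | P(X ≥ cut-off), p = 10% (power) |
|---|---|---|
| ≥ 13 | 11.86% | 91.96% |
| ≥ 14 | 6.87% | 87.06% |
| ≥ 15 | 3.74% | 80.57% |
| ≥ 16 | 1.91% | 72.58% |

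The first cut-off that holds the error at or below 5% is 15, and its power is 80.6%. The last cut-off with at least 85% power is 14, and its error is 6.9%. No row has both.

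**3. Could any other test rescue the pair?** A test that rejects at 15 or more, and at 14 with the probability that brings the error to exactly 5%, is the most powerful at that level. That probability is (0.0500 − 0.0374)/(0.0687 − 0.0374) = 0.403. Its power is 0.8057 + 0.403 × (0.8706 − 0.8057) = 0.832. Even this theoretical test reaches only 83.2%.

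**4. Test and interval.**

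| Changed decisions | Score p | Exact one-sided p | 90% Wilson lower limit | 90% Clopper-Pearson lower limit |
|---|---|---|---|---|
| 13/180 | 0.086 | 0.119 | 4.64% | 4.32% |
| 14/180 | 0.044 | 0.069 | 5.08% | 4.76% |
| 15/180 | 0.020 | 0.037 | 5.53% | 5.21% |

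The Wilson limit always agrees with the score test, because it is that test inverted. It disagrees with the exact test only at 14/180. That outcome has probability 0.0687 − 0.0374 = 3.1% if the true proportion is 5%, and 0.8706 − 0.8057 = 6.5% if it is 10%.

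**5. For scale.** The smallest n with an exact error of at most 5% and power of at least 85% is 199 (reject at 16 or more: 4.27% and 85.2%).

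**The case against.** The best defence is that the plan is coherent as a score-test design. The 85% follows from the document's own inputs by a standard formula. The Wilson interval is the inversion of the score test, and a two-sided 90% interval is the right partner for a one-sided 5% test. On that reading test and interval never conflict, and true power is 87.1%, above what is claimed. Quoting nominal error and large-sample power from standard software is common practice, and naming the test is something a protocol article may leave to the analysis plan.

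Most of this stands, and it limits the point. A reader might infer an arithmetic error; the documents do not support that, since the figure reproduces. A reader might also infer that the planned test and interval contradict each other. They would do so only under an exact test, which the document never names, and then only at one outcome. Nor do the two shortfalls add up: a given cut-off has the excess error or the reduced power, never both. Any further loss of power from patients without a post-EUS plan would rest on an attrition rate that the article does not give, so it forms no part of this point.

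What does not stand is the idea that the analysis plan can settle the matter by naming the test. Naming the score test leaves the stated 5% untrue, and naming the exact test leaves the stated 85% untrue. The sentence in the sample size section needs correcting either way.

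**Conclusion.** The concern holds in a limited form. The sample size section presents, as properties of the design, a pair that no cut-off at 180 patients has. The size is modest: 6.87 − 5 = about 1.9 points of excess type I error under the score/Wilson rule, or 85 − 80.6 = 4.4 points less power under the exact test. It rests on the stated 5% and 10% hypotheses, on all 180 patients being evaluable, and on independent binomial outcomes. It does not undermine the study, and it is a correction worth making rather than one that must be made before the study can proceed.

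**What to change.** State in the sample size and primary analysis paragraphs the number of changed decisions at which the null is rejected, and give the exact type I error and power for that number. Either of two wordings would do.

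- **To hold the stated 5% error rate:** name the exact one-sided binomial test, reject at 15 or more of 180 (8.3%), and restate the design as type I error 3.7% and power 80.6% at a true proportion of 10%. Base any decision read from an interval on an exact 90% limit (4.76% at 14, 5.21% at 15), which agrees with the test. Wilson can still be reported as the interval around the estimate.
- **To keep the score test with the Wilson interval:** state that rejection is at 14 or more of 180, and disclose a true type I error of 6.9% and power of 87.1%.

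The first is preferable if the 5% is meant as a limit. Its cost is a stated power about 4 points lower. The second costs an openly higher error rate. Both change wording only, with no extra patients or data. If the cut-off depends on the number of evaluable patients, give the rule (the smallest count with an exact tail probability of at most 5% under the null) alongside the figure for 180.

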### Qualitative study

#### Objective

To explore factors that influence clinicians and patients’ decision-making about whether EUS should be used.

#### Methods

In parallel to the observational study, semi-structured interviews will be conducted remotely (over the telephone or by video call) as per participant preference.

#### Patient interviews

##### Recruitment

Patient interviews will be up to 60 min with up to 30 trial participants who have optionally consented to interviews. Patients will be invited (via information sheet and informed consent form) to participate in an optional interview in conjunction with the observational study. Following the sampling criteria for the observational study, patients will be contacted by the qualitative researcher anytime between consent and 6 weeks after EUS by phone or email (patient preference) to provide an opportunity to ask questions and confirm willingness to participate before scheduling an interview. Consent will be confirmed prior to interview recording.

##### Eligibility criteria

Capacity to consent.Consented to participate in the observation study.Patients who underwent EUS in the last 6 weeks.

##### Sampling

Purposive sampling of up to 30 patients from participating sites will be interviewed to reach information of power. Interviews will initially be with locally advanced (T2+ and/or N1+) patients. If information of power is deemed to be reached prior to 20 interviews, sampling will subsequently be directed to early-stage patients to compare similarities and differences between groups. If information of power is not reached prior to 20 interviews, sampling will focus on late-stage patients only to optimise the depth and transferability of findings. A conscious effort will be made to sample patients from ethnic minority backgrounds from the baseline demographic data collected in the eCRF as they are known to be currently under-represented in cancer research.

#### Data collection

For reporting purposes demographic data including age, sex, ethnicity, and index of multiple deprivation factors (e.g., post code and education level) will be collected at interview. Interviews will be scheduled prior to treatment initiation or early in the first neoadjuvant chemotherapy cycle (usually 4-6 weeks after EUS) and completed up to 6 weeks after EUS to mitigate the attrition of memory. This approach has been supported by patient and public representatives.

A topic guide has been developed to explore patients’ experiences and factors influencing acceptability of EUS. The interview will focus on patient’s understanding of EUS, their experience of the procedure, and perspectives on how widely they feel it should be used. Patient interviews will commence before clinician interviews so that themes can be presented and discussed with clinicians to understand if/how the information might impact their EUS related decision-making.

Data from all centres will be analysed together and published as soon as possible. A detailed statistical analysis plan will be developed prior to database lock, and all data and appropriate documentation will be stored for a minimum of 25 years after the completion of the trial.

### Clinician interviews

#### Recruitment

Clinician interviews will be up to 30 min with up to 30 clinicians who have consented to interview. The following recruitment strategies will be used to identify eligible participants.

Invite investigators from recruiting sites.An invitation email with the participant information sheet (PIS) will be sent to clinicians (identified by the CI and co-apps) eligible to participate.Ask investigators to identify other eligible cliniciansClinicians may cascade information and pass on contact details to the qualitative interviewer or share the contact details of the interviewer.Advertise through appropriate networks including other UK NHS sites, who the research team already have links and through the specialist societies and Royal Colleges.

